#### EQ-5D-5L (Appendix 2)

The EQ-5D is a standardised measure of health status developed by the EuroQol Group in order to provide a simple, generic measure of health for clinical and economic appraisal.

The survey includes 5 health outcome domains that can be summarised into a utility score.

These include:

- Mobility
- Self-care
- Usual Activities
- Pain/Discomfort
- Anxiety/Depression

There are five descriptive sentences under each heading and patients are directed to tick one box that best describes their health on that day. There is also a visual analogue scale (VAS) that addresses health state.

### Oxford Hip or Knee Scores (Appendix 3)

The Oxford hip (OHS) and knee (OKS) scores were developed in the mid-1990s. The scores were developed to assess the outcome of hip and knee replacements as well as shoulder surgery (including shoulder replacement) and were designed to be completed by patients in order to minimise potential bias. Both two instruments include 12 questions to assess a patient's capacity to undertake general activities of daily living, about their affected hip or knee.

### Pre-operative anticoagulation use (Appendix 4)

Questions listed below will be presented pre-operatively to determine any history of VTE and current use of Anti-coagulant medications. The questions were reviewed and approved by consumer representatives and will be specific to the medications and the site of DVT.

1. Do you normally take (or are you currently taking) blood thinning medication routinely?
2. Do you know what blood thinning medication you are taking?
3. Have you ever been diagnosed with a clot in your legs (Deep Vein Thrombosis - DVT) or lungs (Pulmonary Embolism - PE)?
4. When did your most recent (or only) clot in your legs (Deep Vein Thrombosis - DVT) or lungs (Pulmonary Embolism - PE) occur?

### Post-operative VTE symptoms and occurrence (Appendix 4)

The following questions will be presented post-operatively at both 90 days and 6 months to gauge patient's surgery outcome. Questions 1 to 5 are only specific for the 90 days data collection point and will not be asked on the 6 months data collection point.

1. Did you take your post-surgery blood thinning medication (to avoid blood clots) after leaving hospital following your joint replacement operation?
2. Do you know what blood thinning medication you were taking?
3. How many days did you take the blood thinning medication after your (HIP/KNEE) replacement operation?
4. Since your joint replacement surgery, have you been diagnosed with a blood clot in your legs (Deep Vein Thrombosis - DVT) or lungs (Pulmonary Embolism - PE)?
5. Since your joint replacement surgery, have you had any serious bleeding from anywhere in your body not related to your joint replacement?
6. Have you had any further surgery on your replaced joint (apart from when it was put in)?
7. Please select the reason(s) for the additional surgery/surgeries (select all that apply)

### 3.9. Sample size

A recent large cohort study of 1900 THA and TKA patients from 19 institutions across Australia showed an incidence of symptomatic VTE within 90 days of THA and TKA of 2.6% (manuscript under preparation). A recent randomised trial of aspirin versus rivaroxaban used a minimum clinically important difference of 1%, based on a survey of thromboembolism experts and orthopaedic surgeons.

For the sample size calculation in the CRISTAL study, we used an estimated overall event rate of 2% (a conservative estimate based on the recent Australian cohort study and the current available literature), the same non-inferiority margin of 1% from the recent randomised controlled trial (for aspirin compared to LMWH, 2.5% for aspirin and 1.5% for LMWH), a power of 90% and a one-sided significance level of 0.025. For an individual randomised trial, this yields a sample size of 4,117 per treatment group or a total of 8,234 patients. For a cluster randomised crossover trial, the sample size must account for correlations within clusters during the same time period (intracluster correlation) and between study periods in the same cluster (interperiod correlation). Assuming an intracluster correlation of 0.01, an interperiod correlation of 0.008 and 31 clusters, the sample size required increases to 11,160 patients. From each cluster, we will aim to recruit minimum of 251 registered patients from each group (a total of 15,562 patients), which will allow a 27% loss to follow-up.

Due to uncertainty around the exact event rate and to allow for a smaller non-inferiority margin, we have constructed a sample-size table (Table 1) to demonstrate that the trial will be adequately powered using a non-inferiority margin of 1%, for an event rate up to 3% at 80% power and for an event rate up to 2% at 90% power, provided that loss to follow-up is less than 17%. As a secondary measure, after 1,000 patients have completed the 90-day follow-up, we will obtain a preliminary symptomatic VTE rate for the whole sample and a loss to follow-up rate (without performing any comparative statistical analyses and maintaining blinding) to determine whether the estimates for the primary event rate (2%) and loss to follow-up rate (27%) are accurate and adjust the sample size accordingly if the primary event rate is greater than 3%, whilst accounting for loss to follow-up.

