### **Power and sample size**

For the sample size calculation in CRISTAL, we used an estimated overall event rate of 2% (based on the current available literature) [18, 19], a non-inferiority margin of 1% (based on clinician opinion and a recent randomised controlled trial) [12], i.e., an event rate of 2.5% for aspirin and 1.5% for LMWH, a power of 90% and a one-sided significance level of 0.025. For an individual randomised trial, this yields a sample size of 4,117 per treatment group or a total of 8,234 patients. For a cluster-randomised crossover trial with an intracluster correlation of 0.01, an interperiod correlation of 0.008 and 31 clusters, the required sample

size is 11,160 patients, or 180 patients per arm for each cluster [20, 21]. However, due to the uncertainty surrounding the event rate and intracluster and interperiod correlations, loss to follow-up, uneven recruitment rates leading to unequal cluster sizes or clusters dropping out of the study, we aimed to register 251 patients eligible for the primary objective of the study, providing a total of 15,562 patients. This figure allowed for a maximum 27% reduction in the above sample size calculation [15], however, actual loss to follow-up was expected to be less than this.

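### The 2% event rate is called conservative but is the optimistic choice under a fixed 1% margin, the quoted 2.5%/1.5% rates are the non-inferiority null boundary, and the 3% re-estimation trigger does not hold 80% power at the planned 27% loss

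*Supplement*

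**What the plan says.** Final protocol section 3.9 (Sample size) reports that a cohort of 1,900 Australian hip and knee patients "showed an incidence of symptomatic VTE within 90 days of THA and TKA of 2.6"%. It then states: "we used an estimated overall event rate of 2% (a conservative estimate based on the recent Australian cohort study" and on other literature. The margin is "the same non-inferiority margin of 1% from the recent randomised controlled trial", glossed as "for aspirin compared to LMWH, 2.5% for aspirin and 1.5% for LMWH", with "a power of 90% and a one-sided significance level of 0.025". The final SAP (Power and sample size) repeats the 2% without calling it conservative, and explains the margin as "i.e., an event rate of 2.5% for aspirin and 1.5% for LMWH".

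The result is 4,117 per group for individual randomisation and 11,160 in total for 31 clusters. The registration target of 251 per cluster and arm (15,562) allows for 27% loss.

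The next paragraph of section 3.9 qualifies this. With the 1% margin, power is 90% for rates up to 2% and 80% for rates up to 3%, provided loss is under 17%. A blinded check after 1,000 patients will look at the pooled event rate and the loss, and will "adjust the sample size accordingly if the primary event rate is greater than 3"%, taking loss into account.

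**The concern.** Three statements do not fit the design.

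- **Direction.** With an absolute margin and rates this low, the variance p(1−p) rises with p, and the required sample rises with it. A rate set below the cohort's makes the trial smaller, so it is not a cautious choice.
- **Assumed truth.** The quoted rates differ by exactly the margin. Read as the true rates, they describe a trial in which aspirin sits on the non-inferiority boundary. The alternative at which 90% power is claimed is nowhere stated.
- **Trigger.** A flat 3% threshold matches the claim of 80% power up to 3%. That claim requires loss below 17%, while the same section plans for 27%.

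At stake is whether the stated power can be taken at face value at the one local event rate the protocol cites, and whether the blinded check would act before power fell below the protocol's own lower level.

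**Working it through.** **Inputs** (protocol 3.9 and Table 1): one-sided alpha 0.025 (z = 1.960), power 90% (z = 1.282), margin 0.01, K = 31 clusters, ICC 0.01, interperiod correlation 0.008, 251 registered per cluster-period, 27% loss.

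**1. The plan's own figures.** The superiority formula with pooled variance, for 2.5% v 1.5%:

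n = [1.960·√(2·0.02·0.98) + 1.282·√(0.025·0.975 + 0.015·0.985)]² / 0.01² = (0.3881 + 0.2536)² / 0.0001 = 4,117 per group, an exact match.

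Cluster-period size: m = n(1 − ICC)/(K − n(ICC − IPC)) = 4,117·0.99/(31 − 4,117·0.002) = 179.03, rounded up to 180; 180·62 = 11,160, also exact. The same two steps reproduce all 17 rows of Table 1.

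**2. The non-inferiority calculation.** With a true rate of 2.0% in both arms:

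n = 2·0.02·0.98·(1.960 + 1.282)²/0.01² = 4,119 per group, against 4,117. If the true rates were 2.5% and 1.5%, margin minus true difference would be 0.01 − 0.01 = 0, and the chance of declaring non-inferiority would be 2.5%.

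**3. Direction.** Table 1 at 90% power and a 1% margin gives 11,160 at 2% and 15,190 at 2.5%. At 2.6% in both arms, n = 2·0.026·0.974·10.507/0.0001 = 5,322 per group. Then m = 5,322·0.99/(31 − 5,322·0.002) = 258.8, rounded up to 259; 259·62 = 16,058 analysed, more than the 15,562 to be registered.

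**4. Power by event rate and loss.** Effective n per arm = 31m/(1 + (m − 1)·0.01 − m·0.008). Power = Φ(0.01/√(2p(1 − p)/n_eff) − 1.960), true difference zero.

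| Loss | m analysed | n_eff | p = 2.0% | p = 2.6% | p = 3.0% |
|---|---|---|---|---|---|
| 27% | 183 | about 4,185 | 90% | 82% | 76% |
| 17% | 208 | about 4,590 | 93% | 85% | 80% |
| 10% | 226 | about 4,857 | 94% | 87% | 82% |
| 0% | 251 | 5,215 | 95% | 89% | 85% |

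**5. Where power is lost.** Solving the same expression for p at 27% loss, power falls below 90% above about 2.03% and below 80% above about 2.74%. At 17% loss the 80% point is about 3.0%, which is where the protocol's trigger sits.

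**The case against.** The protocol discloses most of this itself. The paragraph after the calculation confines 90% power to rates up to 2%, and Table 1 gives the larger numbers needed above that. A reader might infer that the plan claims 90% power at the cohort's rate, or hides the loss. The documents do not support that: 82% at 2.6% lies inside the 80–90% band the protocol describes.

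The 82% also depends on the full 27% loss. The final SAP treats 27% as a maximum that also covers uneven recruitment and cluster drop-out, and expects actual loss to be smaller. At 17% loss, power at 2.6% is 85%. This stands, so the 82% must always be quoted with its loss.

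The 2.5%/1.5% pair can be read as illustrating the margin around a 2% average. A reader might infer that the trial has only 2.5% power. The documents never claim power for that truth, and the sample size is right to within two patients per group. The fault is one of labelling.

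Nor does the cohort refute 2%. A simple binomial 95% interval around 2.6% in 1,900 patients is 2.6% ± 1.96·√(0.026·0.974/1,900), or 1.9% to 3.3% before allowing for clustering, and the protocol cites other literature as well. That makes 2% a possible rate, but still not a conservative one.

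On the trigger, wanting it to defend 90% power would be a design preference. At 17% loss, 3% is the right threshold for 80% (251·0.83 = 208 against the 207 in Table 1). The instruction to account for loss governs the size of the adjustment, but the stated condition for making one remains a rate above 3%.

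**Conclusion.** The point holds, at minor severity.

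- Calling 2% conservative is backwards under a fixed absolute margin, by the protocol's own Table 1.
- The 2.5%/1.5% rates in both documents are the null boundary. The alternative that supports 4,117 is equal true rates of about 2.0%; the effect on the sample size is negligible.
- At the protocol's own 27% allowance, power is 90%, about 82% and 76% at event rates of 2.0%, 2.6% and 3.0%. Between about 2.74% and 3% it is under 80% and no adjustment is triggered.

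These figures assume one common event rate in both arms, the plan's ICC and interperiod correlation, equal cluster sizes and the normal approximation the plan itself uses. A t reference on 29 degrees of freedom lowers the three figures by about 2 to 3 points, to 88%, 79% and 74%.

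**What to change.** - **Protocol 3.9:** delete the word conservative. The SAP needs no change here.
- **Protocol 3.9 and SAP, Power and sample size:** state that power is calculated at equal true rates of 2.0% in both arms (true difference zero) against a 1% margin. If 2.5% v 1.5% is kept, label it as the margin at a 2% average.
- **Power statement:** give power at 2.0%, 2.6% and 3.0% by loss to follow-up, as in the table above (at 2.6%: 82% at 27% loss, 85% at 17%).
- **Blinded check:** define the trigger as the pooled event rate at which the protocol's own 80% minimum is lost at the observed loss. That is about 2.74% at 27% loss and about 3.0% at 17%.

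The cost is small. The wording changes need no patients. The stated power looks less favourable, and the trigger could fire somewhat earlier if loss is high. Because the SAP records that recruitment ceased in December 2020, the changes now mainly correct the stated design basis.

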**Table 1 – Sample Size Table for the CRISTAL Trial † ‡**

| Event rate in experimental | Event rate in control | Overall event rate | Non inferiority margin | N in each group (individual) | Cluster size (for 31 clusters) | N total (cluster randomised) |
|----------------------------|-----------------------|--------------------|------------------------|------------------------------|--------------------------------|------------------------------|
| Power = 0.8         |                       |                    |                        |                              |                                |                              |
| 0.015                      | 0.005                 | 0.01               | 0.01                   | 1553                         | 56                             | 3472                         |
| 0.02                       | 0.01                  | 0.015              | 0.01                   | 2319                         | 88                             | 5456                         |
| 0.025                      | 0.015                 | 0.02               | 0.01                   | 3076                         | 123                            | 7626                         |
| 0.03                       | 0.02                  | 0.025              | 0.01                   | 3826                         | 163                            | 10106                        |
| 0.035                      | 0.025                 | 0.03               | 0.01                   | 4567                         | 207                            | 12834                        |
| 0.04                       | 0.03                  | 0.035              | 0.01                   | 5301                         | 258                            | 15996                        |
| 0.0125                     | 0.005                 | 0.00875            | 0.0075                 | 2420                         | 92                             | 5704                         |
| 0.015                      | 0.0075                | 0.01125            | 0.0075                 | 3104                         | 124                            | 7688                         |
| 0.0175                     | 0.01                  | 0.01375            | 0.0075                 | 3784                         | 160                            | 9920                         |
| 0.02                       | 0.0125                | 0.01625            | 0.0075                 | 4461                         | 201                            | 12462                        |
| 0.0225                     | 0.015                 | 0.01875            | 0.0075                 | 5134                         | 246                            | 15252                        |
| Power = 0.9         |                       |                    |                        |                              |                                |                              |
| 0.015                      | 0.005                 | 0.01               | 0.01                   | 2079                         | 77                             | 4774                         |
| 0.02                       | 0.01                  | 0.015              | 0.01                   | 3103                         | 124                            | 7688                         |
| 0.025                      | 0.015                 | 0.02               | 0.01                   | 4117                         | 180                            | 11160                        |
| 0.03                       | 0.02                  | 0.025              | 0.01                   | 5121                         | 245                            | 15190                        |
| 0.015                      | 0.0075                | 0.01125            | 0.0075                 | 4154                         | 182                            | 11284                        |
| 0.0175                     | 0.01                  | 0.01375            | 0.0075                 | 5065                         | 241                            | 14942                        |

† A one sided  $\alpha = 0.025$  is required for a 95% CI. The number of clusters is assumed to 31, the ICC = 0.01 and the IPC=0.008.

‡ Table does not account for an estimation of loss to follow-up

### 3.10. Recruitment

Hospitals will be approached individually by the lead CI and the study team, as appropriate. A site will be considered eligible if they can recruit 251 eligible patients (for the primary analysis for each group) with an aim to recruit this number within 12 months. Departmental (or surgeon group) agreement with the study protocol and the individual treatment protocols (for each group) will be required. Sites where a subgroup of attending surgeons agree to participate will be included if the number of eligible patients for that group of surgeons per year is at least 250. A site investigator will be nominated for each site

### 3.11. Randomisation

Each site will be randomised with a 1:1 allocation with a computer generated random sequence. Simple randomisation will be used (no use of blocks, no stratification). The allocation will refer to the first intervention.

### **3.12. Blinding**

Sites will not be blinded to group allocation. Patients will be aware of a study comparing different treatments for VTE prevention but will not know the specific details of the study and will therefore be blind to the specific interventions and outcomes of the trial such as whether they are in the intervention or control group and the secondary outcomes of the trial. Outcomes will be self-reported with verification of the primary outcome by the Outcome Verification Committee. Where outcome reporting is by phone (back up for failure to capture patients reported outcomes electronically and where verification is performed), those outcome assessors will be blinded to group allocation.

The Outcome Verification Committee will be presented with deidentified cases for assessment. The statistical analysis will be blinded. The Writing Committee will be blinded and will prepare separate manuscripts based on the possible group allocations.

### **3.13. Data collection**

Data collection for baseline data and follow-up at 90 days and 6 months will be patient-reported electronically (via tablet, phone or computer) using direct data entry. For patients not responding to email and SMS follow-up, telephone contact will be used to administer the surveys verbally.

#### Pre-Operative

When collected electronically by patients, data will be directly entered into the AOANJRR Clinical Trials Platform.

Some patients may not have direct access to the internet. This is especially a factor for older patients and patients from lower socioeconomic groups. Another group who could potentially be excluded from implementing this approach to data collection are non-English speaking patients. To overcome these barriers patients will be given the option to nominate a 'proxy' e.g. family member or friend to assist them with completing the instruments and receive reminders electronically on their behalf. Information will be collected on whether the patient had assistance to complete the CRISTAL questions and these data will be reviewed during the analysis.

There will be various methods and procedures implemented at the different hospitals to register patients and request them to complete the CRISTAL data online. Ideally the patients will complete pre-operative CRISTAL data immediately when first approached, however, this may not always be possible. There is functionality built into the system to email a patient the link to the website to complete the CRISTAL requirements at a time that is convenient for them.

Some hospitals participating in CRISTAL already routinely collect PROMs and wish to continue to do so using their own systems. In these cases, the AOANJRR will work with the hospital to simplify the data collection process and avoid duplication of collection. A data sharing agreement will be entered into between the hospital and the AOANJRR whereby data can be exported from the current system and imported into the AOANJRR Clinical Trials Platform. There will be a secure file sharing facility established within the web application to

ensure secure transfer of confidential information. The data provided will be reviewed by the data manager prior to upload into the database to confirm quality and completeness.

#### Post-Operative

Follow-up will be by telephone until the electronic data capture system is built and telephone follow-up will be used as back up for the electronic follow-up once in place. Patients will be able to login and complete their 90-day follow-up from 75 days and 6-month follow-up from 5 months.

The Arthroplasty Clinical Outcomes Registry (ACORN) has been contracted to complete the follow-up phone calls. ACORN was selected because this Registry already collects PROMs centrally for hospitals, predominately in NSW, and the staff have expertise in this area.

### **3.14. Data management**

Data quality will be checked monthly under the supervision of the Data Quality Committee.

### **3.15. Statistical analysis**

The analysis for the primary objective will be limited to patients undergoing elective primary THA or TKA for a diagnosis of OA, excluding patients for whom the study drugs were contraindicated (e.g., allergy or need for alternative anticoagulant – warfarin, NOAC, dual antiplatelet, for a pre-existing condition). This analysis will test between-group difference in the proportion of cases developing VTE within 90 days for non-inferiority of aspirin at a margin of 1%, on an intention to treat basis.

The primary analysis will use cluster summary methods. These methods estimate the treatment effect using cluster level differences and have been shown to be appropriate for cluster randomised crossover trials with rare outcomes and the intracluster and interperiod correlation coefficients expected in this trial.

Multiple imputation to account for missing outcome data will be investigated, using auxiliary variables gathered from routine AOANJRR data (including age, sex, baseline health, pain and function, diagnosis and surgical factors). Since VTE is rare, if prediction in the imputation models using these auxiliary variables is a problem, no imputation will be performed due to the possibility of bias. Since the most likely reason for loss to follow-up is difficulty in contacting patients postoperatively (rather than any association with treatment assignment or outcome), missing outcome data is expected to be missing completely at random, which will not cause bias in the estimates.

Secondary analyses will be performed for the primary outcome, to test for differences in treatment effect between subgroups of patients: THA only, TKA only and bilateral joint replacement. The analysis method will be the same as the primary outcome and will include an interaction term between subgroup and treatment group.

Further secondary analyses will include an extension of the primary analysis for patients undergoing all forms of HA and KA (total, revision, partial) for any indication (non-elective surgery, non-OA diagnoses) and will include patients for whom the study drug was

contraindicated. This will assess the effect of implementing the protocol at a departmental (hospital) level. Other secondary analyses will include an analysis of the subcategories of VTE as the outcome; PE only, all DVT, above knee DVT only and below knee DVT only and non-VTE related complications (death, re-operation, major bleeding and readmission rates). Cluster summary methods will be used for all secondary analyses.

If aspirin is found to be inferior to LMWH, a cost effectiveness analysis of aspirin compared to LMWH will be performed from a health system perspective. Data for resource use associated with treatments and complications will be taken from trial data within the AOANJRR. Survival at one year and quality of life measured using EQ5D at baseline and six months will allow calculation of differences in quality adjusted life years (QALYs) between groups. We will calculate the cost per QALY for each treatment comparison as the difference in mean costs divided by the difference in mean outcomes (quality adjusted survival as QALYs) over the duration of the trial, using regression analysis to adjust for differences at baseline and clustering by site.

